Pre-test and post-test counseling are essential for HIVST, facilitating linkage to care and behavioral change among HIVST users. In standard-of-care HIV testing and counseling (HTC), the pre-testing counseling involves assessing the individual's risks, providing information about HIV testing, asserting the user's right to refuse the test, and informing the user about the possibility of beneficial disclosure of sero-status status, as well as providing preventive information and material. Post-test counseling entails interpreting testing results, offering psychological support to individuals with positive results, facilitating beneficial disclosure of positive sero-status, and referring individuals for further care, treatment, and support services. Additionally, preventive information and material are provided for those with negative test results. Despite the advantages of HIVST, HIVST users may skip pre-testing or post-test counseling. There are concerns about incorrect procedures, inadequate support for users, and potential issues related to the linkage of care. A meta-analysis study examined that HIVST reduced linkage to care by 47% comparing facility-based HIV testing due to the lack of counseling support.

In previous projects, an evidence-based HIVST service was developed for MSM in Hong Kong, which included online promotion of HIVST, delivery of free HIVST kits, and provision of online real-time instruction and standard-of-care pre-test/post-test counseling via live chat application (HIVST-OIC). The HIVST-OIC is highly effective in increasing HIVST uptake and the proportion of HIVST users receiving counseling along with testing. A randomized controlled trial (RCT) showed that after being offered HIVST-OIC, 87.9% of participants took up HIVST, and all HIVST users received counseling. Moreover, the HIVST-OIC was effective in reducing sexual risk behaviors among users. The Centre for Disease Control and Prevention (CDC) listed HIVST-OIC as an evidence-based intervention and best practice. However, there are issues during the implementation, as HIVST-OIC requires intensive resources. Therefore, it is difficult to increase the service capacity of HIVST-OIC, resulting in a significant gap in implementation.

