## Objectives

This study aims to demonstrate whether an innovative HIVST service with online real-time instruction and counseling provided by a fully automated Chatbot (HIVST-Chatbot) is as efficacious, if not more efficacious, as HIVST-OIC in increasing HIVST uptake and the proportion of HIVST users receiving counseling alongside testing among MSM in Hong Kong.

The primary objective is to establish whether HIVST-Chatbot would produce effects similar to HIVST-OIC in increasing HIVST uptake and the proportion of HIVST users receiving counseling alongside testing within a six-month follow-up period. We hypothesize that HIVST-Chatbot would be statistically non-inferior to HIVST-OIC in increasing HIVST uptake and the proportion of HIVST users receiving counseling alongside testing. The non-inferiority margin is set as 10% (HIVST-Chatbot is no worse than 10% less than that of the HIVST-OIC). The secondary objectives are to compare HIVST-Chatbot with HIVST-OIC on the prevalence of condomless anal intercourse (CAI), multiple male sex partnerships, and uptake of HIV testing other than HIVST at Month 6.

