### **Sample size planning**

The target sample size is 528 (264 per group). Our previous study showed that about 90% of MSM used HIVST after exposure to HIVST-OIC promotion and implementation. We conservatively assume that 80% of participants in the control group will take up HIVST during the project period. A non-inferiority margin of between-group difference of this primary outcome is set at 10% (no worse than 10% less than that of the control group). A sample size of 198 per group will be sufficient to confer 80% power at the one-sided significance level of 0.05 (PASS 11.0). Given the 25% drop-out rate during the follow-up period, 264 participants per group (528 total) will be needed for the study.

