## Statistical analysis

Intention-to-treat analysis will be performed. Multiple imputations will handle missing values at Month 6. Markov Chain Monte Carlo method will be used to impute data with the arbitrary pattern of missing values, while monotone methods are used to impute data having a monotone pattern of missing values. Predictors included baseline background characteristics and baseline values of these outcomes. The relative risk reduction, absolute risk reduction, and number needed to treat, and their 95% confidence interval will be calculated using Excel. The chi-square tests will inspect between-group balances of potential confounders at baseline. Adjustments will be made if any potential confounders show  $P < .05$  in the comparisons. SPSS 26.0 for Windows (SPSS Inc., Chicago, IL) will be used for all analyses; statistical significance is set at the  $P < .05$  level (one-sided).

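### The protocol's single one-sided 5% significance level fits the primary non-inferiority tests but not the secondary comparisons, for which no direction or margin is stated

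*Protocol*

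**What the plan says.** The closing sentence of the protocol's Statistical analysis section names the software and then the significance rule: "will be used for all analyses; statistical significance is set at the" P < .05 "level (one-sided"). No other level or sidedness is given for any outcome in that section.

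The same section plans relative and absolute risk reductions and numbers needed to treat with 95% confidence intervals. It does not say whether the intervals are one- or two-sided, or which outcomes they cover. It also plans chi-square tests of baseline balance, with adjustment triggered at P < .05.

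A direction is stated only for the primary outcomes. Under Objectives: "We hypothesize that HIVST-Chatbot would be statistically non-inferior to HIVST-OIC". Under Sample size planning: "A non-inferiority margin of between-group difference of this primary outcome is set at 10" percentage points, and "A sample size of 198 per group will be sufficient to confer 80% power at the one-sided significance level of 0.05 (PASS 11.0").

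For the secondary outcomes, Objectives says only: "The secondary objectives are to compare HIVST-Chatbot with HIVST-OIC on the prevalence of condomless anal intercourse (CAI), multiple male sex partnerships" and testing by other routes. The Secondary outcomes section defines these variables and attaches no hypothesis, direction or margin to them.

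**The concern.** A one-sided test is defined only once its side has been fixed. For the primary outcomes the non-inferiority hypothesis fixes it. For the secondary outcomes nothing in the protocol does, yet the only significance rule on the page is one-sided.

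Either sign would matter for risk behaviour. The Background section reports that "the HIVST-OIC was effective in reducing sexual risk behaviors among users", so replacing the human administrator with an automated service could lose part of that benefit. The Discussion and Conclusions propose taking the Chatbot into routine services if it is non-inferior on the primary outcomes, so readers will look to the secondary results for reassurance on risk behaviour. For HIV testing by other routes it is not even clear which direction counts as favourable.

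**Working it through.** **1. The one-sided level belongs to the primary test.** Inputs from Sample size planning: control uptake 80% ("We conservatively assume that 80% of participants in the control group will take up HIVST during the project period"), margin 0.10, one-sided 0.05, power 80%, drop-out 25%. Equal uptake in the Chatbot group is implied, not stated.

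- n per group = (1.645 + 0.842)² × (0.8×0.2 + 0.8×0.2) / 0.10² = 197.8, rounded up to 198.
- 198 / (1 − 0.25) = 264 per group, 528 in total.

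Both figures match the protocol, so the one-sided 0.05 is consistent with the test it was sized for.

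**2. The same rule on a secondary comparison, by how the side is settled.**

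- *Side chosen after seeing the data.* The test rejects when |z| > 1.645. False-positive error = 2 × 0.05 = 0.10. A two-sided 5% test rejects when |z| > 1.960, with error 0.05.
- *Side fixed as Chatbot better.* The error is 5%, but an increase in risk behaviour falls in the tail that is never tested.
- *Side fixed as Chatbot worse.* The error is 5% and the test looks for harm, but it cannot flag a benefit.

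**3. Illustration for condomless anal intercourse.** The protocol gives no rates, so these are assumptions: control 30%, 40% or 50%, and Chatbot 10 points higher. The probability of significance uses the normal approximation with SE = √[p₀(1−p₀)/n + p₁(1−p₁)/n].

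Worked case, 40% against 50% with n = 198: SE = √[(0.24 + 0.25)/198] = 0.0497, so 0.10/SE = 2.010.

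- One-sided 5%, side Chatbot better: Φ(−2.010 − 1.645) = 0.00013.
- One-sided 5%, side Chatbot worse: Φ(2.010 − 1.645) = 0.643.
- Two-sided 5%, increase detected: Φ(2.010 − 1.960) = 0.520.

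Range over the three assumed control rates:

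| Test | n = 198 per group | n = 264 per group |
|---|---|---|
| One-sided 5%, side Chatbot better | 0.00009 to 0.00013 | 0.00002 to 0.00004 |
| One-sided 5%, side Chatbot worse | 64% to 68% | 75% to 78% |
| Two-sided 5% | 52% to 56% | 64% to 68% |

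**4. Test against interval.** A two-sided 95% interval is the estimate ± 1.960 SE, so it includes no difference whenever |z| < 1.960. The one-sided 5% test is significant from z = 1.645. Between the two, where the one-sided P is .025 to .05, the test is significant and the interval includes no difference. Example: at z = 1.80 the one-sided P is .036, while the lower limit is 1.80 SE − 1.96 SE = −0.16 SE.

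**5. Balance tests.** The chi-square statistic takes no account of sign, so a one-sided level has no natural meaning for these tests either.

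**The case against.** The strongest reply has four parts.

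*Scope.* A reader might infer that the protocol expressly prescribes one-sided testing for every analysis. It does not: the words about all analyses govern the software, and the significance clause after the semicolon carries no scope words. It could have been written with only the primary test in mind, since it matches the level in Sample size planning. This stands as a point of grammar. The clause is nevertheless unrestricted and the protocol offers no other rule for secondary outcomes, so someone following it would apply it to them.

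*Error.* A reader might infer that the secondary error rate is doubled outright. It is not: with a side fixed in advance the error is 5%. The 10% arises only if the side follows the data, and the protocol does not say that it will. An analysis plan, which is not at hand, could fix the side. If that side were Chatbot worse, the one-sided test would be more sensitive to harm than the two-sided one, as the table shows. This also stands, but the protocol states no side, and that choice would leave a benefit untestable.

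*Harm.* A reader might infer that an increase in condomless sex would be hidden. The risk reductions and 95% intervals are not confined to the primary outcomes; if they are two-sided and given for these outcomes, an increase would appear as a negative risk reduction. Under the side Chatbot better, harm is out of reach of the significance test, not of every output.

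*Multiplicity.* A reader might compute the chance of at least one false positive over seven comparisons as 1 − 0.90⁷ = 52%. That assumes independence, treats the five testing venues as separate tests, and takes the 10% case throughout. Two-sided testing would still give 1 − 0.95⁷ = 30%, so much of it is multiplicity and not sidedness. The documents do not support it as the size of this problem.

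**Conclusion.** The point holds in a limited form. The protocol's only significance rule is one-sided, and its secondary comparisons have no stated direction or margin, so the rule does not fit them. The supportable size is up to 10% rather than 5% false-positive error per secondary comparison, on the condition that the side follows the data. Alternatively, if the side is fixed as Chatbot better, the significance test has practically no chance of flagging an increase in risk behaviour (about 0.0001 or less for a 10-point rise under the assumed rates). These are alternatives, and the protocol does not settle which applies. The disagreement between test and interval rests on the 95% intervals being two-sided and reported for these outcomes.

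The choice of a one-sided 5% level for the primary test is not part of this point. The primary conclusion, the margin and the sample size are untouched; only claims about secondary outcomes are affected.

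**What to change.** In the last sentence of Statistical analysis, state that the one-sided 5% level applies only to the non-inferiority tests of the two primary outcomes. Add that secondary outcomes will be reported as risk differences with two-sided 95% confidence intervals, tested at two-sided 5% and labelled exploratory. Limiting the one-sided level in this way also frees the baseline balance tests from it.

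The cost is a short edit to one sentence and slightly less favourable secondary P values: a result at z = 1.80 moves from one-sided .036 to two-sided 2 × .036 = .072. The 198 and 264 per group and the primary analysis stay as they are.

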## Results

Study recruitment will start in April 2023, and data collection is expected to be concluded in January 2024. No results are available as of manuscript preparation.

## Discussion

The COVID-19 pandemic and its control measures (e.g., lockdown, closure of business, physical distancing) have direct and negative impacts on HIV testing service utilization among MSM, especially for facility-based HIV testing services. Across countries, health authorities have been actively promoting HIVST to mitigate such negative impacts. As a result, there was an increase in HIVST use among MSM. Such growth may continue even in the post-pandemic era. Therefore, ensuring sufficient support and linkage to care for the increasing number of MSM HIVST users becomes more important. Although evidence-based HIVST services existed (e.g., HIVST-OIC), most required intensive resources to implement and maintain. Such constraints limited their public health impacts. To our knowledge, this is the first attempt to apply an artificial intelligence Chatbot to deliver real-time instruction and counseling support to HIVST users. This RCT will compare the efficacy of the HIVST-Chatbot with an evidence-based HIVST service, the HIVST-OIC, in increasing HIVST uptake and the proportion of HIVST users receiving counseling along with the testing. If HIVST-Chatbot is proven non-inferior to HIVST-OIC in improving HIVST uptake and coverage of counseling among users, it may address the existing HIVST service gaps. Since HIVST-Chatbot is fully-automated and requires fewer resources to implement and maintain, it can be promoted and implemented by governmental organizations and CBOs in Hong Kong as an alternative approach to HIVST-OIC. The HIVST-Chatbot has the potential to overcome the barriers to using HIVST (e.g., concerns about lack of support and missing linkage to care), improve overall HIV testing coverage, and reduce the HIV burden among MSM.

Although the trial will yield essential insights for HIVST program planning and policymaking, it has some limitations. First, the use of HIV testing other than HIVST-Chatbot or HIVST-OIC is self-reported. Such responses may be over-reported due to social desirability. Second, similar to most interventional studies, participants will be recruited through convenient sampling. Caution should be taken when generalizing the findings to MSM in Hong Kong. Third, collecting characteristics of MSM who refuse to participate in the study is difficult. Selection bias may exist.

## Conclusions

This study will generate important research and policy implications regarding using Chatbot in HIVST services. If HIVST-Chatbot is proven non-inferior to HIVST-OIC, it can be easily integrated into HIVST services provided by the governmental organization and CBOs in Hong Kong. The coverage of HIV testing and the level of support to HIVST users will be vastly increased.

